### 2.2. Patient and Public Involvement

Participants will be recruited when receiving hospital care. Inclusion criteria will be (1) participants must be adolescents from 12 to 16 years of age, with (2) a diagnosis of CD (endocrinologic, such as DM1, or pneumo allergic diseases) within the last 6 months. Exclusion criteria will be (1) the presentation of a psychiatric disorder prior to the disease; (2) epilepsy, infantile cerebral palsy, or brain tumours; and (3) not understanding the Spanish language. All the parents of recruited adolescents will be offered the opportunity to participate in shorter sessions to promote self-care and family bonding. The parent training will be conducted in two 2-h sessions. The trainers will be psychologists specialised in health psychology who, prior to the start of the program, will receive hours of training in the 10Vida program.

### 2.3. Interventions

10Vida is a program that consists of different psychological objectives to be applied to adolescents between 12 and 16 years of age who suffer from a chronic disease thatincludes the pneumo allergic or endocrinological specialties. It is a 7-session intervention programme (five individual sessions with adolescents, and two sessions with family caregivers) consisting of one session per month with patients, and two sessions at the end of the treatment with family caregivers (month 4 and month 5).

It is a program that provides strategies and tools, trying to provide answers to the needs of the adolescent and caregivers, which can facilitate adherence to treatment and, therefore, improve physical and psychological health. It has been shown that a psychological intervention is necessary in addition to the important medical treatment, as it improves the emotional well-being of the adolescent and their families. 10Vida consists of individual sessions for both adolescents and their families, such as parents as caregivers who may be overloaded with tasks, worries, and the need to help their child to be happy. The specific objectives of each of the adolescent and caregiver sessions, as well as the areas to be worked on, are shown in Table 2. In addition, a summary of the strengths promoted by the programme are shown in Figure 1. To work on the different session objectives, various activities or tasks have been developed with different objectives to improve each of the key areas of the sessions. All activities can be found in Table 3. Participants who do not complete 80% of the sessions will be excluded from the study.

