## Abstract

Suffering from a chronic disease (CD) in adolescence can significantly impact the emotional health of adolescents and their families. MHealth can be a useful tool for these groups. However, few intervention programmes include the family system. The aim is to design an intervention programme (10Vida) for a paediatric population with a CD, and their families, to improve their adaptation to the disease. The study is a quasi-experimental repeated measures design in a open study, where the patients themselves, and their families, are their own control group. Participants will receive an intervention of seven individual sessions: five sessions with each patient, and two sessions with their caregivers. In the case of the patients, the aim is to improve their emotional state, their self-esteem, and their emotional competencies, reducing their perceived threat of illness. Furthermore, in the case of the caregivers, the aim is to improve their emotional state and reduce their burden. Indirectly, working with caregivers and those being cared for will improve family ties. The pilot study will involve 25 to 30 chronically ill adolescents aged between 12 and 16 years and their primary caregivers. Following the results, the necessary modifications will be included, and the programme will be offered to adolescents and their families who are willing to participate.

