### 2.1. Study Setting

This study will be conducted in the different leading hospitals of the Valencian Community, in the Pneumology, Endocrinology, and Allergology units. This study is a quasi-experimental design with repeated measures. Each participant receiving the intervention (experimental condition)will also act as their control grorup. Therefore, the physical and psychological diagnostic measures will be collected from all of participants in an initial assessment (T1) and, secondly, six months after the initial assessment and right before starting the treatment programme (T2). At these two assessment points (T1 and T2), all participants (patients and family members) will be assessed (T2). The treatment lasted for five sessions for adolescents, with one individual session per month and two sessions for family caregivers (month 4 and month 5). The treatment programme will begin in the maximum expected time of 15 days from the second pre-treatment assessment (T2), with an estimated duration of 5 months. After the end of the treatment sessions for the patient and their family members, a new diagnostic test (T3) will be conducted (across all variables), within an expected maximum time of 15 days until the end of the treatment, to assess the post-treatment change. Thus, the estimated time between T1 and T2 is the same as that between T2 and T3, which is six months. The programme of registration, interventions, and evaluations (SPIRIT Programme) is shown in Table 1 and Table S1. 

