#### Statistical Methods

Independent-samples *t*-tests and chi-square tests were performed to determine pre-intervention differences between participants with and without missing values in the variables studied. In addition, chi-square tests were undertaken to compare the number of people who dropped out of the research in the experimental group with those who dropped out in the control group, and it was found that they did not differ significantly.

Before testing the change models, descriptive analyses, Pearson correlations, and multivariate and univariate variance analyses (MANOVA and ANOVA) were performed with the pre-intervention scores of the participants in the experimental and control groups to identify possible differences in the baseline. Likewise, multivariate and univariate covariance analyses (MANCOVA and ANCOVA) were performed to identify changes in the post-intervention scores (short-term effect), while controlling for the pre-intervention scores (covariate). In addition, the effect size (Cohen’s *d*) of each variable was calculated to estimate the magnitude of the differences between the experimental and control groups. These analyses were performed with the statistical package SPSS V.26.

Multiple hierarchical regression analyses were conducted to examine the added predictive value of the experimental condition to explain the effectiveness of the intervention programme [46]. Firstly, the pre-intervention assessment score (control variable) was introduced, and then the experimental condition (1 = experimental intervention group, 0 = control group) was introduced as an independent variable. The dependent variable was the change variable between pre- and post-interventions, as well as between pre-intervention and the follow-up of the emotional and well-being variables. In this sense, the statistically significant change of the determination coefficient in model 2 (predictor: experimental condition, controlling for the pre-intervention score) is interpreted as an added predictive value. The significant prediction of the experimental condition, controlling for the pre-intervention score, leads us to attribute the significant change to the intervention. All data shall be entered electronically. Participant files will be recorded securely and will be stored for a period of 10 years after the end of the study.

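### Excluding anyone below 80% attendance makes the treatment-period result a completers-only result, and the plan does not say whose sessions the 80% is counted on

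*Protocol article*

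**What the plan says.** Section 2.3 (Interventions) of the protocol article sets the rule: "Participants who do not complete 80% of the sessions will be excluded from the study". The same section describes the programme: "It is a 7-session intervention programme (five individual sessions with adolescents, and two sessions with family caregivers". The Abstract counts sessions the same way: "Participants will receive an intervention of seven individual sessions: five sessions with each patient, and two sessions with their caregivers".

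Section 2.1 treats both patients and family members as participants. It places the sessions after the second assessment and uses each person as their own control: "Thus, the estimated time between T1 and T2 is the same as that between T2 and T3, which is six months". Table 1 marks allocation as not applicable. (Section 2.4 labels the three assessments T0 to T2; T1, T2 and T3 are used here as in section 2.1.)

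On caregivers, section 2.2 says: "All the parents of recruited adolescents will be offered the opportunity to participate in shorter sessions".

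Statistical Methods (section 2.8) describes two checks on losses. One examines "pre-intervention differences between participants with and without missing values in the variables studied". The other is a chi-square comparison of dropout in the experimental and control groups, reported with its result: "and it was found that they did not differ significantly".

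**The concern.** Whether someone reaches 80% is known only after T2, so the set that contributes a T2–T3 change is chosen by what happens during treatment. Families who get little from the programme may be the ones who stop coming. If so, the remaining sample improves on average even when the programme does nothing. There is no separate arm to absorb this, since the treatment effect rests on the T2–T3 change of those who stay. One stated aim (section 1) is to analyse effectiveness, and the programme is then to be taken to a wider clinic population, so the people who stop are part of the question.

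The rule removes people from the study, not merely from one analysis set. T3 data that were never collected cannot be recovered by any later analysis plan.

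Two further points bear on the same sentence. The 80% has no stated denominator, so two sites could apply it differently. And the article already reports that dropout was balanced, which would reassure a reader on exactly this point.

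**Working it through.** **1. What 80% means**

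Inputs: 5 adolescent and 2 caregiver sessions, threshold 0.80 (section 2.3).

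- Over all seven sessions: 0.80 × 7 = 5.6, so 6 are needed.
- Over the adolescent's own five: 0.80 × 5 = 4.
- Over the caregiver's own two: 0.80 × 2 = 1.6, so 2 are needed.

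| Adolescent | Caregiver | Over seven | Seven-session reading | Adolescent, own sessions |
|---|---|---|---|---|
| 5 of 5 | 0 of 2 | 5/7 = 71.4% | removed | kept |
| 5 of 5 | 1 of 2 | 6/7 = 85.7% | kept | kept |
| 4 of 5 | 2 of 2 | 6/7 = 85.7% | kept | kept |
| 4 of 5 | 1 of 2 | 5/7 = 71.4% | removed | kept |

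Illustration on the seven-session reading: if a caregiver attends each session independently with probability c (assumed), the share of fully attending adolescents removed is (1 − c)². That is 25% at c = 0.5, 9% at 0.7 and 1% at 0.9.

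**2. Size of the selection effect**

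The article gives no dropout rate and no link between attendance and outcome, so both are assumed. Let q be the share excluded and r the correlation between the tendency to complete and the T2–T3 improvement, with no true effect and normal distributions. The mean improvement among completers, in SD of the change score, is

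bias = r × φ(z_q) / (1 − q).

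- q = 0.15, r = 0.2: 0.2 × 0.2332 / 0.85 = 0.055
- q = 0.25, r = 0.4: 0.4 × 0.3178 / 0.75 = 0.169
- q = 0.35, r = 0.6: 0.6 × 0.3704 / 0.65 = 0.342

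**3. Consequence for a test with nominal favourable error of 2.5%**

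Section 2.6 gives about 200 adolescents for the main study. Take q = 0.25, r = 0.4, so 150 completers. Selection shrinks the completers' SD slightly, to 0.962.

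- T2–T3 change tested against zero: 0.1695 × √150 / 0.962 = 2.16; Φ(2.16 − 1.96) = 0.58. Simulation gives about 57%.
- T2–T3 change contrasted with a waiting-period change in the same 150 people, of SD 1 and taken as independent: 0.1695 / √((0.926 + 1)/150) = 1.50; Φ(1.50 − 1.96) = 0.32. A simulated regression of change on pre-score and condition, with an assumed between-assessment correlation of 0.5 and everyone's waiting-period rows kept, gives about 29%. Hence roughly 30%.
- At q = 0.15, r = 0.2 (170 completers), simulation gives about 12% for the simple test and 8% for the regression; the closed form above gives 11% and 7%.
- With 28 enrolled (inside the 25–30 pilot range) at q = 0.25, r = 0.4: about 12% for the simple test and 7–8% for the contrast.

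**4. The dropout statement**

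Everyone passes through the waiting period and then the programme. An independent-groups chi-square test of dropout needs two separate sets of people, and the design has one. The main study is scheduled for September 2022 to September 2024 (section 2.5) and had not run when the result was written down.

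**The case against.** Several stronger readings are tempting and are not supported.

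- *The rule removes adolescents who attended all their own sessions.* The seven-session count has support in the Abstract and section 2.3, but section 2.1 treats patients and family members each as participants, which fits counting each person's own sessions. On that count no adolescent at 5 of 5 is removed. Even over seven, removal needs a caregiver at 0 of 2. What stands is that the denominator is undefined.
- *The result is certainly biased towards benefit.* The article does not establish this. Adolescents who feel better may also stop attending. The direction depends on an assumed positive link between attendance and improvement.
- *Nothing in the plan would show the problem.* Statistical Methods does compare pre-intervention scores of people with and without missing values. That is a real check on selective loss, but it cannot show how the excluded people changed after T2.
- *Excluded families stay in the control data.* The wording more naturally removes all of a person's data. It is not explicit either way.
- *The 57% is the error rate of the planned analysis.* It belongs to a simple test of T2–T3 change. Statistical Methods compares experimental with control condition, for which roughly 30% is nearer.
- *The balanced-dropout result is invented.* A six-participant pilot ended in January 2020 (section 2.5), and the past-tense sentence cannot be dated. Losses can also be described by period. Only the comparison of independent groups is inapplicable.

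A separate analysis plan may exist, but it could not restore T3 data from people already put out of the study.

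**Conclusion.** The concern holds for the stated exclusion rule. As written, the T2–T3 effect is conditional on completing at least 80% of sessions, and the article names no all-starters analysis to set beside it. This should be changed before the main study, because T3 data not collected are lost.

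The size rests on assumed dropout and correlation. With no true effect, the false improvement is about 0.17 SD in the middle scenario and 0.05 to 0.34 SD across the range. The inflation of favourable false positives is material with 200 enrolled even at the mild end. If attendance were unrelated to improvement, this bias would vanish.

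The undefined denominator is a second, certain defect, though its effect depends on how often caregivers attend neither session. The dropout sentence is a real but secondary defect.

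**What to change.** - Replace the exclusion sentence in section 2.3 with: participants who stop attending remain in the study and are asked to complete T3.
- Make everyone who started the programme the primary analysis set, with a method that uses all available assessments. A mixed model is one example; the choice can be left to the analysis plan.
- Use 80% attendance only to define a supplementary set. Count it on the adolescent's own five sessions for adolescent outcomes and on the caregiver's own two for caregiver outcomes.
- Delete the dropout result from Statistical Methods. Plan instead to report losses in T1–T2 and in T2–T3 separately, with T1 scores by completion status.

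The cost is wording, plus one more online questionnaire for people who stop early. The estimated effect will probably be smaller than among completers alone.

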### 2.4. Outcomes

All instruments will be completed by the participants during baseline (T0, control), pre-intervention (T1), and post-intervention (T2).

Primary patient outcomes
*Emotional adjustment:* Hospital Anxiety and Depression Scale (HADS): For the study of anxiety, depression, and global emotional distress [59] (scale validated for the Spanish adolescent population) [60]. In terms of psychometric properties, the reliability scores in the study with adolescents were 0.80;*Emotional competence:* Emotional Skills and Competence Questionnaire (ESCQ-21): This is a self-report measure developed by Takšić [61] to assess emotional competence. In the present study, the reduced version (ESCQ-21) was used, which was adapted and validated to a Spanish sample by Schoeps et al. [62]. Psychometric properties are adequate (perception and comprehension, α = 0.82; expressing and labelling, α =0.90; and management and regulation, α = 0.77);*Perceived illness threat* (BIP-Q) [63,64]: Assesses the patient’s perceived level of disease threat with their symptom control, associated emotions, the duration of the disease, and the causes or factors of the disease. Psychometric properties are adequate (α = 0.76);*Self-esteem:* Rosenberg Self-Esteem Questionnaire (RSE) [65]: Self-esteem was assessed using the Spanish version of this scale [66]. In terms of psychometric properties, the reliability scores in the original study were 0.92;

Primary caregiver outcomes
*Emotional adjustment*: Hospital Anxiety and Depression Scale (HADS): for the study of anxiety, depression, and global emotional distress [59]. Regarding the scale’s internal consistency, a validation study in a Spanish adult population found that values for the anxiety scale ranged between 0.68 and 0.93, and for the depression scale, between 0.67 and 0.90;*Burden or stress*: The Paediatric Inventory for Parents (PIP) [6] to assess levels of caregiving-related stress [6,67]. It aims to assess parents’ stress with children requiring regular medical care. It consists of 12 situations related to the hospital environment that are considered potentially stressful for parents with ill children. Optimal reliability coefficients were obtained, with 0.78 for the total frequency scale and 0.81 for the total stress scale [6].

Secondary patient outcomes
*Adaptation to chronic disease:* The Chronic Respiratory Disease Questionnaire (CRQ-SAS) [68] assesses aspects related to the adaptation to the disease (scale validated for the Spanish adolescent population by Valero et al. [69]). The psychometric properties are adequate (α = 0.85). The questionnaire on the adaptation to type 1 diabetes (RAE) [70] assesses aspects related to the adaptation to the disease, such as severity, adherence, psychological impact, discomfort, and health behaviours. Psychometric properties are adequate (α = 0.77). Finally, the Adolescent Rhinoconjunctivitis Quality of Life Questionnaire (AdolRQLQ) [71] is a quality of life assessment instrument specifically designed for the paediatric population with rhinoconjunctivitis. This questionnaire shows adequate psychometric properties (α = 0.77);*Parenting style of parents*: The Scale for the Evaluation of the Educational Style of Parents of Adolescents (EP) [72] allows for the assessment of the perception that adolescents have of their parents’ educational style;*Psychological well-being*: The Psychological Well-Being Scale for Adolescents (BIEPS-J) is a self-report measure developed [73] to determine the level of psychological well-being in adolescents (scale validated for the Spanish population [74]).

In addition to the psychosocial variables, objective measures, such as those obtained through medical indicators, were considered as secondary variables:*Glycaemic control:* Glycosylated haemoglobin (HbA^1^c) will be used to assess the glycemic control of the diabetic patient;*Somatometry to assess nutritional status:* Weight, height, body mass index (BMI), the brachial perimeter, and the tricipital fold will be used, with the calculation of percentiles and the z-score. To assess nutritional status, weight-for-height percentiles, BMI, or z-scores will be used. The aim is to maintain weight-for-height or BMI at the 50th percentile, as well as height/age (which is the best sign for disease control);*Spirometry values:* This will be used to determine pulmonary function. Spirometry is a test that studies pulmonary functions under controlled circumstances, as well as the absolute magnitude of lung volumes, and the speed with which the patient can mobilise them. The main spirometric parameters recorded are forced vital capacity (FVC), vital capacity (VC), peak expired air volume in the first second (FEV1), and peak expiratory flow (PEF);*Analytical controls:* This will be used (a) for monitoring nutritional status (protein, lipids, fat-soluble vitamins, iron and calcium-phosphorus metabolism) and Quick’s index; (b) for monitoring exocrine pancreatic function (faecal elastase and steatorrhoea); (c) for monitoring glucose metabolism; (d) for monitoring acute phase reactants and the immune status (immunoglobulins and alpha1 antitrypsin; and (e) for monitoring hepatic and renal functions;*Control images:* Using computerised axial tomography (CAT) or X-rays, the aim was to control the evolution of the disease through the appearance of bronchiectasis (small scars in the lung) or other types of pulmonary affections.*Others* (according to age): a) Plestimography values, whichdetect static lung volume, and b) bone densitometry, when there are risk factors for skeletal demineralisation.

Secondary caregiver outcomes
*Resilience:* Connor–Davidson Resilience Scale (CD-RISC-10) [75] to assess the ability to cope with stress and adversity. The CD-RISC-10 is a shortened version of the CD-RISC [76];*Family functioning:* The Family Cohesion and Adaptation Scale (CAF-R) (FACES) [77]) will be used. It was developed to construct a measuring instrument to evaluate the variables that make up the dynamics of a family, based on Olson’s Circumplex Model. The scale consists of two dimensions: cohesion, understood as “the emotional bond that exists between family members” and family adaptability, that is, “the family’s capacity to change and adapt to change”.

All these variables would be assessed if sufficient participants were obtained. If not, the researchers would only use the primary variables for statistical analyses.

### 2.5. Participants’ Timeline

The first pilot study started in February 2019, following the proposed structure with a small sample of six participants (adolescents and their families), and it was concluded in January 2020. Due to the pandemic, this protocol had to be adapted to a fully online format while maintaining the activities and variables studied. Currently, the February 2022 participants are being recruited for a second pilot study to test the intervention and improve the programme. The main study is scheduled to run from September 2022 to September 2024. Table 1 shows the timeline for the enrolment, interventions, and evaluations. The main objectives of phase I are the selection of the hospitals, the request for informed consent, and the baseline assessment. Firstly, the services of the hospitals that the research team has convened will be contacted. After meetings with the directors, informed consent will be requested from the families and adolescents participating in the programme. Before implementation, patients will be asked to complete a set of questionnaires. Phase II’s main objective is to evaluate the participating patients and family members, as they will constitute the control group. After six months, in phase III, the main objective will be implementing the intervention programme in the same sample as in phase II. After completing the intervention, in phase IV, participants will be re-evaluated. In the last phase, the effectiveness of the programme will be analysed.

